## Abstract

**Background:**

Patient outcomes following low-trauma hip fracture are suboptimal resulting in increased healthcare costs and poor functional outcomes at 1 year. Providing early and intensive in-hospital physiotherapy could help improve patient outcomes and reduce costs following hip fracture surgery. The HIP fracture Supplemental Therapy to Enhance Recovery (HIPSTER) trial will compare usual care physiotherapy to intensive in-hospital physiotherapy for patients following hip fracture surgery. The complex environments in which the intervention is implemented present unique contextual challenges that may impact intervention effectiveness. This study aims to complete a process evaluation to identify barriers and facilitators to implementation and explore the patient, carer and clinician experience of intensive therapy following hip fracture surgery.

**Methods and analysis:**

The process evaluation is embedded within a two-arm randomised, controlled, assessor-blinded trial recruiting 620 participants from eight Australian hospitals who have had surgery for a hip fracture sustained via a low-trauma injury. A theory-based mixed method process evaluation will be completed in tandem with the HIPSTER trial. Patient and carer semi-structured interviews will be completed at 6 weeks following hip fracture surgery. The clinician experience will be explored through online surveys completed pre- and post-implementation of intensive therapy and mapped to domains of the Theoretical Domains Framework (TDF). Translation and behaviour change success will be assessed using the Reach Effectiveness-Adoption Implementation Maintenance (RE-AIM) framework and a combination of qualitative and quantitative data collection methods. These data will assist with the development of an Implementation Toolkit aiding future translation into practice.

**Discussion:**

The embedded process evaluation will help understand the interplay between the implementation context and the intensive therapy intervention following surgery for low-trauma hip fracture. Understanding these mechanisms, if effective, will assist with transferability into other contexts and wider translation into practice.

**Trial registration:**

ACTRN 12622001442796.

**Supplementary Information:**

The online version contains supplementary material available at 10.1186/s13063-024-08143-4.

## Background

Hip fractures are common, increasing in incidence, and have a high burden for patients and the health system. Globally, the incidence of low-trauma hip fractures—typically seen in people with osteoporosis—is anticipated to increase from 1.6 million in 2000 to 4.5 million by 2050 [1]. A large component of the increased burden can be attributed to prolonged hospital length of stay [2]. With an ageing population and increasingly complex care needs, additional research is needed to optimise patient care and improve patient outcomes following hip fracture surgery.

Current evidence demonstrates poor functional outcomes following hip fracture despite prolonged inpatient rehabilitation and significant cost to the healthcare system. In some jurisdictions, the average total length of stay exceeds 30 days [2], and only 24% of patients regain their pre-fracture mobility at 120 days post-fracture [3, 4]. There are significant ongoing costs as a result of hip fractures for the patient, their family and the healthcare system [5].

There is some evidence to suggest that early and intensive rehabilitation in the acute setting could provide opportunities to improve recovery and reduce hospital length of stay following hip fracture [6]. However, current care guidelines for the management of patients following hip fracture do not specify intensity of physiotherapy, reflecting a lack of robust evidence to guide practice [7, 8]. The current HIP fracture Supplemental Therapy to Enhance Recovery (HIPSTER) trial aims to address this evidence gap by conducting a multi-site, double-blinded, randomised controlled trial (RCT) comparing usual care to intensive in-hospital physiotherapy [9]. The HIPSTER trial will follow Medical Research Council (MRC) recommendations for developing and evaluating complex interventions [10]. It will include a process evaluation embedded within the trial with the aim of facilitating research translation within the clinical setting.

The HIPSTER Trial is an Australian Medical Research Future Fund (MRFF) supported trial. It is a two-arm, assessor-blinded randomised controlled trial. A detailed protocol has been published [9] with an overview of key trial design elements presented here. A sample of 620 participants will be recruited from 8 acute hospitals in Australia. To be eligible for inclusion, participants must be aged ≥ 65 years old, be able to mobilise pre-operatively, admitted from home with an isolated subcapital or intertrochanteric hip fracture, suitable for surgical management (including fixation or arthroplasty). For patients unable to provide informed consent due cognitive impairments, consent will be requested from the person responsible for their medical decisions. Consenting participants will be randomised 1:1 to either usual care (physiotherapy as usually provided by that site) or intensive physiotherapy in hospital over the first 7 days following surgery (two additional sessions per day, one delivered by a physiotherapist and the other by an allied health assistant). The aim of intensive physiotherapy is to progress the functional gains achieved in the usual care session as documented in the participant’s medical record. The allied health assistant will aim to practice exercises and functional mobility from the usual care physiotherapy session. A 7-day period was selected as this is the median length of stay in the acute care setting in Australian hospitals [3]. The primary outcome of the HIPSTER trial is total hospital length of stay. Secondary outcomes include clinical outcomes and healthcare costs in the 12 months following hip fracture. The sample size calculations allow for 10% attrition and are based on the primary outcome measure and the results from the phase II trial [6]. Alfred Health Human Research Ethics Committee has approved the protocol for the main trial and this process evaluation (Project ID 8840, local reference 441–22).

### The process evaluation

Implementing intensive physiotherapy following hip fracture requires a system change in usual practice for physiotherapists, allied health assistants and patients. It also requires workforce and other resourcing adjustments. Therefore, it is important to understand barriers and facilitators to implementation of intensive therapy following hip fracture from multiple perspectives. The complexities of the intervention and setting lend itself to completing a theory-based process evaluation in parallel with the HIPSTER clinical trial [10]. This will help identify how the intervention interacts with contextual factors [11] and how these vary across each of the eight sites. A recent update by the MRC identified understanding the implementation context as an important goal in establishing intervention effectiveness [11]. Research into intensive therapy for other conditions (such as stroke) provide insight into what implementation barriers may exist following hip fracture surgery. The A Very Early Rehabilitation Trial after stroke (AVERT) identified key implementation barriers such as staffing, team challenges and organisational barriers [12]. Patient barriers unique to the acute hospital setting included medical stability, severity of condition and participation in therapy [12]. Completing a theory-based process evaluation will expand our understanding of how and why intensive physiotherapy is effective or not effective and therefore aid translation into management of patients following hip fracture surgery [13].

The implementation context and problem inform the following assumptions about effective implementation of the intervention (see Fig. 2). Firstly, intensive physiotherapy improves patient functional outcomes, and this improvement will result in a shorter length of stay. Secondly, it is assumed the staff delivering the intensive therapy have the necessary skills and knowledge to effectively deliver the additional sessions, and it will be feasible to deliver the intensive therapy for at least 4 days in the acute hospital.

### Aims

The aim of the process evaluation embedded within the HIPSTER trial is to support the interpretation of trial outcomes and inform future scale up and facilitate delivery in clinical practice. The process evaluation will answer the following questions:To what extent was intensive physiotherapy delivered to intervention group participants in the first 7 days following hip fracture?What factors are associated with effective implementation of intensive physiotherapy following hip fracture?What barriers and facilitators exist for implementation of the intervention, from the perspectives of healthcare professionals, and the patients who were offered the intervention?How likely is intensive physiotherapy following hip fracture surgery to be sustainable and what factors will enable sustainable translation into clinical practice within the acute hospital setting?

## Methods

The MRC recommendations used to conceptualise the complex intervention components includes applying a theory-based approach to guide the process evaluation. We will apply two theoretical frameworks: the Theoretical Domains Framework (TDF) [14] and Reach Effectiveness, Adoption, Implementation and Maintenance (RE-AIM) [15], to analyse results and synthesise findings from qualitative and quantitative data collection methods. The study design and timepoints of measurement are in Fig. 1 and Table 1.

**Fig. 1 Fig1:**
[figure not shown]
Process evaluation design and conduct. mILOA, Modified Iowa Level of Assistance Score; EQ-5D-5L, EuroQol 5D-5L; ICECAP-O, ICEpop CAPability measure for Older people; short FES-I, Short Falls Efficacy Scale—International

**Table 1 Tab1:** Schedule of trial follow-up and procedures

Assessment/procedure	Baseline	Day 7	Hospital discharge	6 weeks	120 days	12 months
Informed consent	X					
Demographic information and baseline outcomes	X					
Total hospital length of stay			X			
mILOA		X				
EQ-5D-5L and ICECAP-O		X		X	X	X
FES-I		X		X	X	X
Remain in hospital				X		
Return to preadmission mobility				X	X	X
Current residence				X	X	X
Reoperation rate				X	X	X
Discharge destination from the acute ward			X			
Adverse events (including readmissions, falls)				X	X	X
Healthcare utilisation				X	X	X
Economic evaluation						X
Implementation						X

*mILOA* Modified Iowa Level of Assistance Score, *EQ-5D-5L* EuroQol 5D-5L, *ICECAP-O* ICEpop CAPability measure for Older people, *short FES-I* Short Falls Efficacy Scale—International, *MBS/PBS* Medicare Benefits Schedule and Pharmaceutical Benefits Scheme

To determine translation and behaviour change success of HIPSTER, the RE-AIM framework will be applied. This framework effectively evaluates public health interventions by assessing outcomes against five key dimensions: Reach, Effectiveness, Adoption, Implementation and Maintenance [16]. We will report on all domains across individual and organisational levels, where appropriate [15, 16]. The outcomes assessed (Table 2) include participant characteristics, participation rates, intervention completion, intervention effectiveness and characteristics of staff delivering the intensive physiotherapy. Key outcomes will be reported and analysed according to the clinical protocol [10]. Categorical data will be summarised in counts and percentages, with numerical data summarised as either means and standard deviations or medians and interquartile range depending on distribution of data. Qualitative data will be analysed using thematic analysis. The TDF will be applied to understand individual behaviour change success. The TDF is a framework combining different theories of behaviour change to identify factors affecting healthcare professional behaviour and guide more targeted implementation interventions [17]. It will be used as a coding framework to understand clinician responses to the pre- and post-implementation surveys [14, 18].

**Table 2 Tab2:** RE-AIM elements and outcomes assessed

RE-AIM element	Outcomes assessed
Reach	Percent of eligible individuals who participate Characteristics of participants and non-participants (age, insurance status, postcode, pre-fracture residence, walking ability and cognitive status)
Effectiveness	Clinical outcomes, healthcare utilisation, adverse events Patient and carer experience (semi-structured interviews)
Adoption	Characteristics of staff delivering intervention, health care professional experience (surveys), clinical partner involvement
Implementation	Number of intensive physiotherapy sessions delivered, components delivered, adaptations made to intervention, total physiotherapy time
Maintenance	Individual: patient outcomes at 12 months (e.g. quality of life), factors supporting the participant’s recovery Organisation: intent to continue the intervention at 6 months post-trial completion, local funding models, modifications made, intervention intensity provided to patients

*RE-AIM* Reach, Adoption, Implementation and Maintenance

### Process evaluation design and conduct

A mixed methods study design will be undertaken in parallel to the HIPSTER trial to evaluate the process of HIPSTER at the intervention level, patient and carer level and clinician level.

#### Intervention level

To determine translation at an intervention level, the RE-AIM framework will be applied. A site initiation visit will be completed, providing education about current evidence, existing gaps in the literature and aims of the HIPSTER Trial. No additional training will be provided for staff delivering the intervention. The intervention therapy delivered will be determined by the physiotherapist’s assessment of the individual patient. The physiotherapy review will aim to progress functional gains achieved in the usual care session including increasing independence with mobility, gait aid progression and increasing walking distance. The allied health assistant review will practice achievements gained during the usual care review. The key difference in management between usual care and the intervention group is the increased frequency of physiotherapy and allied health assistant sessions. There should be no change to usual care with all discharge and follow-up determined by usual practices at the site. We will assess any changes to usual care over the course of the trial, including changes to clinician behaviours. Sites will maintain an intervention log for each participant randomised to the intervention group. Staff delivering the intervention will complete it at the end of each session. The intervention log will contain the number of intervention sessions delivered per resource (Physiotherapist or Allied Health Assistant), the duration of the session (minutes) and a brief description of the intervention provided (e.g. ambulation, exercises). Any missed intervention sessions will be documented, and an explanation provided. These data will track intervention fidelity and be summarised by percentage of planned sessions delivered. Intervention completion will be defined as those that received their designated therapy for at least 4 days in the acute hospital.

The key components of the intervention assessed by RE-AIM are outlined in Table 2. The *reach* of the intervention will be determined by the percentage of eligible participants who participate and their characteristics. Intervention *effectivenes*s will be evaluated by clinical outcomes (Table 1 and Fig. 1) as explained in our trial protocol [9], adverse events and patient experience (semi-structured interviews with questions focussing on the perceived effect of the intervention). The primary clinical outcome is total hospital length of stay (days). Secondary clinical outcomes include functional mobility assessed by the Modified Iowa Level of Assistance Score (mILOA) and completed on day 7 following surgery; health-related quality of life and falls efficacy will be assessed at all follow-up timepoints and measured through EuroQol 5D-5L (EQ-5D-5L), ICEpop CAPability measure for Older people (ICECAP-O) and Short Falls Efficacy Scale—International (FES-I). Healthcare utilisation and the associated costs will be collected through monthly phone calls with the participant, and the collection of health systems costs from Health Services Australia Data (incorporating Medical Benefits Schedule and Pharmaceutical Benefits Scheme) over the 12-month follow-up period. Adverse events as defined by GCP standards will include hip and non-hip related in-hospital and out-of-hospital events. The *Adoption* of the intervention including health care professional characteristics, experience and perspectives of intensive therapy will be gathered through pre- and post-clinician surveys. We will record intervention completion, the number and components of the intervention delivered including total physiotherapy and allied health assistant time and adaptations made for *implementation*. *Maintenance* at an individual level will be measured by patient outcomes across at 12 months following surgery (e.g. quality of life measured using EQ-5D-5L) as well as the participant and carer experience of the intervention and the factors supporting their recovery. *Maintenance* at an organisational level will be measured by intention to continue delivering the intervention at 6 months following trial completion, including local funding models and modifications made, and the intensity of the intervention delivered.

#### Participant and carer level

Clinical outcomes and their collection method are explained in detail in our published protocol [9]. Eligible patients will be approached to consent to the trial during the perioperative phase. They will be included if they fulfil the following criteria: age $$\ge$$ 65 years old, admitted from home with a hip fracture (either subcapital or intertrochanteric) and managed surgically. They will be excluded if they were unable to mobilise (with or without a gait aid prior to the surgery) and are not allowed to full-weight-bear or weight-bear-as-tolerated. Once consented, baseline data will be collected at hospital admission with key follow-up assessment timepoints occurring at day 7, 6 weeks, 120 days and 12 months following surgery. At initial study consent, participants or their proxy decision-maker will be invited to participate in semi-structured interviews at 6 weeks following surgery. At the 6-week review with the blinded assessor, participants or their carers will be asked if they consent to be contacted by an experienced qualitative researcher who is independent of the site clinical and research staff. Those who consent and are eligible (have recall of the acute inpatient hospital admission) will be contacted to participate in a semi-structured interview. The participants will be asked about their experience of intensive therapy and their recovery and discharge from hospital as well as barriers and facilitators to participation in the intervention, with an interview guideline developed using RE-AIM framework (supplementary material A). Interviews will be conducted via the telephone, at a time of the participant’s preference. A sampling framework will be applied to ensure diversity across hospital, gender and presence of a carer. Interviews will be transcribed verbatim within 6 weeks of completion of the interview. All participant discussions and responses will be coded to ensure participants cannot be identified from their responses. Two researchers will independently undertake line by line analysis of the coded transcripts, to generate descriptive themes [19]. The two researchers will refine the descriptive codes into themes and subthemes through iterative discussion [20]. Representative quotes from participants will be used to illustrate the identified themes. Interviews will continue until data saturation is reached, i.e. when no new themes emerge from consecutive interviews.

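### Seeking interview permission in the blinded assessor's 6-week review puts assessor blinding at avoidable risk for later secondary outcomes

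*Protocol article*

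**What the plan says.** The section on the participant and carer level describes recruitment to the interviews in three steps.

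- Enrolment: "At initial study consent, participants or their proxy decision-maker will be invited to participate in semi-structured interviews at 6 weeks following surgery".
- Six weeks: "At the 6-week review with the blinded assessor, participants or their carers will be asked if they consent to be contacted". The contact would come from an "experienced qualitative researcher who is independent of the site clinical and research staff".
- Afterwards: "Those who consent and are eligible (have recall of the acute inpatient hospital admission) will be contacted", by telephone.

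On content, "The participants will be asked about their experience of intensive therapy and their recovery and discharge from hospital". The third question under Aims seeks the views of healthcare professionals "and the patients who were offered the intervention".

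The trial overview in the Background describes an assessor-blinded trial of 620 participants randomised 1:1. Table 1 schedules further outcomes at 120 days and 12 months.

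**The concern.** Participants can notice whether they had two extra sessions a day, so the assessor's ignorance of the arm is a main protection against detection bias in outcomes obtained by questioning. The 6-week review is one of the encounters in which that ignorance has to be kept. The plan uses the same encounter to raise an interview whose subject is the treatment that separates the arms.

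An assessor who learns the arm may, without meaning to, prompt, clarify or record differently from then on. At stake are the between-arm comparisons of quality of life, capability, falls efficacy, return to mobility and reported events at the later visits.

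**Working it through.** The article gives no figure to reproduce for this point, so the check sets its statements side by side.

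**1. Who asks, and where.** The request is placed in the review held with the blinded assessor. The sentence is passive, so the assessor is implied rather than named as the one asking. No other staff member is mentioned at that review.

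**2. Who is asked.** The statements point two ways.

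| Statement in the article | Points to |
|---|---|
| Enrolment invitation to participants or proxies, with no arm restriction | both arms |
| Six-week request to participants or carers, with no arm restriction | both arms |
| Interview eligibility: consent and recall of the admission | both arms |
| Sampling by hospital, gender and presence of a carer | both arms |
| Interview topic: intensive therapy, and barriers and facilitators to taking part in it | intervention arm |
| Third aim: patients offered the intervention | intervention arm |

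**3. What each reading implies.**

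- Intervention arm only: being asked identifies the participant as an intervention participant.
- Both arms: being asked carries no information about the arm. What remains is that a participant or carer, already told of the interview at enrolment, mentions the extra sessions in reply.

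**4. Recall.** Read literally, recall is established before the researcher makes contact, but the article does not say by whom. If the assessor does it, the check itself prompts talk about the admission.

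**5. What is still to be measured.** From Table 1 and the section on the intervention level:

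| Outcome | Timing or source | Exposed? |
|---|---|---|
| Total length of stay (primary) | hospital discharge | not materially |
| mILOA | day 7 | no, it precedes the request |
| EQ-5D-5L, ICECAP-O, FES-I | 6 weeks, 120 days, 12 months | yes at the last two; at 6 weeks only if the request comes first |
| Return to mobility, residence, reoperation, adverse events | 6 weeks, 120 days, 12 months | same timing, to the extent obtained by asking the participant |
| Healthcare use by monthly telephone call | caller not stated | only if a blinded assessor makes the calls |
| Medicare and pharmaceutical benefits data | administrative | no |

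**6. Safeguards.** The section on the clinician level delays the second staff survey until after recruitment has ended, expressly to avoid unblinding staff. No comparable protection is stated for the 6-week request: the article gives neither its order relative to the measures, nor its wording, nor a rule that both arms are asked alike.

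**The case against.** The strongest reply is that the literal text sets no arm criterion. Everyone may be asked the same neutral question, with selection by arm made later by someone unblinded, and the request then reveals nothing. All that is sought is agreement to be contacted; the discussion of therapy is kept for an independent researcher. A second approach at 6 weeks also has a purpose: enrolment is perioperative, consent may come from a proxy, and recall of the admission cannot be known then. Finally, question order and scripts are often left to a full protocol.

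Much of this stands. The request cannot be called arm-dependent on the text, and a 6-week re-check is not superfluous. It does not follow that the re-check belongs in the blinded session. Nor is this simply a detail left elsewhere: the article is the protocol for the process evaluation, interview recruitment is its own subject, and it refers to the main protocol for clinical outcomes and their collection. The point concerns a step the article does fix.

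A reader might go further and infer that the request unblinds the whole intervention arm, 620 / 2 = 310 people, and the controls by omission. The documents do not support that. It requires arm-restricted asking, which is only inferred, and asking every intervention participant. Interviews stop at data saturation, are limited to English speakers and need recall of the admission, and the sample size allows for 10% attrition. If many intervention participants were never asked, not being asked would not identify a control. The figure of 310 is a ceiling under one reading, not an estimate.

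It is also fair to say that participants complete the questionnaires knowing what therapy they had, so an unblinded assessor adds less bias there than on an assessor-rated scale.

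**Conclusion.** The concern holds as an avoidable risk to assessor blinding, created by a stated procedure and left without a stated safeguard. It does not show that unblinding will occur.

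- If the request is limited to the intervention arm, it discloses allocation for those asked.
- If it goes to both arms, it does not disclose the arm by itself but gives an opening for disclosure.

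The reach is limited to secondary outcomes reported by participants or collected by interview at 120 days and 12 months, and at 6 weeks if the request comes before those measures. Even this assumes that blinded assessors collect them and that whoever hears the request also does later assessments or passes the information on; the article states neither. The number unblinded and the resulting bias cannot be estimated from the article.

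A reader might infer a threat to the main result or to the whole economic evaluation. The documents do not support that: length of stay and day-7 mILOA are largely or wholly settled before 6 weeks, and administrative cost data do not pass through an assessor. The change is worth making because it is cheap, not because the primary analysis is in doubt.

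**What to change.** Preferred change: take permission to be contacted at initial consent, where the interviews are already raised. After the 6-week measures are complete, have the independent qualitative researcher, or other non-blinded staff, re-confirm willingness and check recall. This keeps the later confirmation and takes it out of the blinded session.

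If the request must stay in that review:

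- make it identically in both arms, after all 6-week measures;
- use a neutral script that does not mention therapy;
- select by arm later, in an unblinded step;
- record any unblinding the assessor reports.

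The article should also say in plain terms whether interviewees come from one arm or both.

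The cost is a small change to procedure and consent wording. No extra staff should be needed, since the independent researcher already contacts interviewees. Interview uptake might fall slightly without a face the participant knows at the 6-week request. The Trial status section reports recruitment as ongoing, so the change could help participants who had not yet reached 6 weeks; for those already past it, recording assessor unblinding at the remaining visits is what is left.
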